# Digitally Enhanced Mentoring for Immigrant Youth Social Capital: Protocol for a Mixed Methods Pilot Study and a Randomized Controlled Trial

**DOI:** 10.2196/16472

**Published:** 2020-03-17

**Keywords:** social capital, e-mentoring, youth mentoring, health promotion intervention, mixed methods, randomized controlled trial, immigrant

## Abstract

**Background:**

There are large disparities between immigrants and native Norwegians in domains such as health, education, and employment. Reducing such disparities is essential for individual and societal well-being. Social capital is associated with positive effects on these domains, and mentoring programs have the potential to boost social capital. However, few studies have assessed mentoring as a social capital intervention among youth or the potential barriers and facilitators of implementing digitally augmented mentoring.

**Objective:**

The goal of this paper is to describe a protocol for assessing the implementation and effectiveness of a digitally augmented mentoring program for immigrant youth as a health intervention to promote social capital. The two-stage analytical framework for a pilot study followed by a randomized controlled trial (RCT) is presented. The pilot aims to assess program fidelity and make necessary intervention adjustments before the RCT. The RCT aims to assess the effects of the implemented intervention program on social capital and the relationship between program fidelity and effects.

**Methods:**

Both the pilot and RCT will use mixed methods with a process evaluation approach used to structure the intervention and a pre-post test survey component to measure social capital and fidelity of program implementation. Interviews will also be used to enrich the quantitative data from the survey.

**Results:**

The pilot study is scheduled to begin in fall 2019. Based on data analyses in spring 2020, potential adjustments will be made to the intervention, with findings used in preparation for the full-scale RCT study.

**Conclusions:**

Digitally enhanced mentoring programs may be a helpful intervention for providing immigrant youth with tools for increasing their social capital and indirectly improving health outcomes. This protocol provides new knowledge about the implementation and evaluation of such programs.

**International Registered Report Identifier (IRRID):**

PRR1-10.2196/16472

## Introduction

### Background and Context

Globally, significant discrepancies exist between immigrant youth and native-born individuals with regards to school dropout, isolation, unemployment, and health. For example, 71% of immigrants in Norway report experiencing at least one of eight listed health problems compared with 49% of the population at large [1]. Relatedly, there is a 26% difference between immigrant and native Norwegian youth with regard to education and employment, with anxiety and depression contributing to these discrepancies [2,3]. These issues also hinder inclusion and integration of new immigrants. Reducing disparities among these vulnerable groups represents an important area of focus, and Norwegian policymakers are increasingly willing to test new approaches.

Social capital, a focus of this study, is associated with a variety of positive health outcomes, including self-reported health [4-6], psychiatric outcomes [7], and mortality [8]. On average, immigrants tend to have less access to certain forms of social capital compared with ethnic Norwegians [9], and investing in social capital can potentially enhance health among immigrant youth. Social capital is multidimensional and has been conceptualized in multiple ways [10-13]. Broadly, it includes relational and cognitive (trust, sense of belonging) and structural (networks or connections among individuals, along with community engagement) dimensions [14]. Analyses can be at the individual or collective level, with focus on different types of social capital: bonding, bridging, and linking [13,15]. With regard to immigrant populations, bonding refers to connection with and support from individuals with a similar ethnic, linguistic, or religious identity, whereas bridging implies connections to those of dissimilar backgrounds, often the majority population [13,16]. Linking relates to vertical relationships between an individual and institutions or individuals in positions of authority [17]. Although bonding social capital is helpful for “getting by,” bridging capital is important for “getting ahead” [13]. Bonding is the most prevalent form of social capital among immigrants [18] and can provide social support and belonging, decrease isolation, and allow sharing of local knowledge [9,19]. Bridging includes benefits, such as increased ability to gather information [20], and can facilitate positive labor market outcomes, such as relevant employment [21]. Both bridging and bonding types are important, and bonding appears to facilitate bridging [22]. Immigrant youth are an important target group for study, as they generally have weaker social capital compared with natives [9,22]. This is exacerbated for the unaccompanied refugees in the group who arrive with no family and lack this important aspect of social capital.

Although approaches for strengthening social capital are clearly worth pursuing, interventions to increase youth social capital, such as the one proposed in this paper, are quite new [23]. Little is known about how such interventions might be implemented, and their effects [24]. Although not systematically studied as such, mentoring programs have the potential to act as “social capital interventions” by assisting immigrants in expanding their networks, and thus their social capital [25,26]. In this setting, mentoring can be defined as “taking place between young persons (ie, mentees) and older or more experienced volunteers (ie, mentors) who are acting in a nonprofessional helping capacity to provide relationship-based support that benefits one or more areas of the mentee’s development” [27]. Participation in youth mentoring programs is associated with improved outcomes across social, behavioral, and academic domains [28]. Such programs, typically conducted by social entrepreneurs, have few traditions in Norway. For the program described in this paper, coordinators recruit, select, train, and match mentors and mentees, and all mentees receive the same basic program. Main program components include training for both mentors and mentees before program start, mentee and mentor sharing of their achievement story (a proud life moment), identification and discussion of mentee strengths, a “roadmap” selecting a goal and describing tasks for the mentee to achieve it, and a network mapping exercise for the mentees. Additionally, the program requires six face-to-face dyad meetings, with one meeting each month during the six-month program period. Staff members also follow up on the matches monthly. Mentees are recently arrived immigrant youth recruited from local schools; willingness and interest in participating are the main selection criteria. Mentor volunteers are recruited in a variety of ways, including personal connections with program staff, social media, and volunteer recruitment websites.

Although one might assume that digital support for this type of mentoring program holds potential for reach and effectiveness, few programs employ digital tools or have been studied systematically [29,30]. Therefore, a prior study [31] of immigrant mentees’ and mentors’ experiences and needs was conducted to guide the development of a digital platform. This platform is integral to the mentoring program described in this protocol. The platform was designed to augment and boost, rather than replace, preexisting mentoring program components. Key elements of the platform include a timeline to provide oversight over dates of program events and show program progress, messaging, cards for identifying personal strengths, a forum for mentees and mentors, a network map, and a toolbox containing helpful supplementary resources (eg, information on writing a good resume). Figures with screenshots illustrating planned iterations of the platform are available in Multimedia Appendices 1 to 4. Although the digital platform is expected to enhance social interactions and program fidelity compared with the program without digital support, the protocol does not directly address this issue.

### Objectives and Significance

This paper describes a protocol for studying a digitally augmented mentoring program as a social capital intervention for immigrant youth in Norway. The protocol proposes a pilot study followed by a randomized controlled trial (RCT). Ultimately, we are interested in assessing the implementation and effects of mentoring program participation on social capital. A process evaluation framework inspired by a previous study [32] will be applied for investigating the implementation of the mentoring program in this pilot study. This framework consists of (1) contextual factors that affect the implementation, (2) what has been implemented and how, and (3) mechanism of impact (ie, the participants’ responses to and interactions with the program). Thus, the objective of the pilot study is to assess program fidelity and design by investigating the context, implementation process, and mechanisms of impact [32,33]. The questions guiding the pilot study are:

What contextual factors affect the implementation?How is the mentoring program implemented (ie, fidelity, dose, and reach)?What are the participants’ experiences in the mentoring program?Are the measures used for studying outputs and outcomes valid, and are they acceptable and meaningful to stakeholders?

The pilot allows adjustments of the social capital intervention before full-scale implementation and the RCT. The intention of the RCT is to investigate the effects of the implemented program on the social capital of immigrant youth, guided by the following questions:

To what extent was the intervention implemented (outputs)?What are the effects of the implemented program on social capital indicators (outcomes)?What is the relationship between program fidelity and effects?

The study offers both theoretical and empirical contributions. First, much of the work related to mentoring as an intervention has been done in the United States, with primarily qualitative studies in the United Kingdom [28]. Therefore, this work will contribute by extending the empirical context. Second, few studies have assessed social capital interventions [34], particularly among youth. More commonly, social capital is used as an independent variable (see [35] for a health intervention to increase social capital among Latinx and black adults). Furthermore, little is known about the implementation and effects of such interventions [23], although research indicates potential in this area [25,35]. This study seeks to address these gaps, providing both theoretical and summative insights. The overall objective is to evaluate the intervention in light of challenges and opportunities in implementation and to explore the effects of this implementation.

### Analytical Framework

The logic model [36,37] depicted in Figure 1 provides a valuable framework for identifying and illustrating the relationship between clusters of variables in the study. The model identifies a problem (youths’ lack of connection to Norway), which requires a response, and specifies activities to address the issue (the mentoring intervention). The implementation of the solution leads to tangible outputs (program delivery) and measurable outcomes (social capital) as the consequence of the outputs; the broader impacts (social inclusion) are the logical effects of the intervention. There is a tight relationship between the identified problem, the intervention, the program outputs, and the outcomes of interest.

**Figure 1 figure1:**

Logic model for the protocol (based on [36,37]).

The pilot study focuses on the first three boxes in Figure 1, allowing adjustments before the RCT if certain outputs are not achieved. The full-scale implementation of the intervention will focus primarily on assessing outputs and outcomes. Impacts are often indirect, and there are significant challenges in causal attribution; thus, impacts are not measured as part of this study. However, the implication is that if outcomes are achieved, broader and more distal societal impacts will result.

The framework depicted in Figure 1 provides a general guide for the study. Research suggests that multicultural youth have narrower networks and less access to certain forms of social capital [9], which contributes to higher dropout rates and poorer health than natives. There is evidence that social capital is associated with improvements in these domains and may facilitate integration and inclusion [4,21].

The mentoring intervention seeks to address these discrepancies. An important focus is on how the program can strengthen mentees’ networks through information exchange and social contact and increase trust and feelings of belonging (social capital). Thus, the study emphasizes outputs and outcomes, as well as the influence of contextual factors on these.

## Methods

### Study Design

The first stage is the pilot study, followed by the RCT. A mixed-methods approach will be used combining quantitative survey instruments (pre-post test design) with qualitative data from interviews and focus groups [38]. The survey will measure outputs (program fidelity, dose, and reach); outcomes (cognitive and structural social capital), which are a result of the implementation outputs; and contextual factors (respondents’ demographics, school characteristics, and usability of the digital platform). Specific cutoffs for assessing fidelity to the core program components (described in the Background and Context section) and effectiveness will be developed based on pilot study results. Interviews with mentors, youth, and program staff will allow a detailed qualitative understanding of the mechanisms occurring and stakeholder experiences.

### Sample and Participant Recruitment

Both stages of the study will be conducted in close cooperation with mentor program staff (the individuals working directly to coordinate, match, train, and follow up on dyads), and with feedback from the youth. The primary unit of analysis for the study is recently arrived immigrant youth, ages 15 to 25 years, attending school. These youth will be in or have completed their first year of Norwegian schooling; therefore, they will have a minimum basic level of Norwegian proficiency. We will offer interviews in Norwegian and English, but will also consider the use of a translator, as necessary, for the RCT to gain a better understanding of the experiences of participants with varying levels of Norwegian language comprehension. Information from mentors and program staff will also be collected. Informed consent will be obtained and the voluntary nature of participation will be emphasized to the youth, with information that they can end their participation at any time. A video will be used to present the research project, handling of data (confidential, but not anonymous), and privacy issues in youth-friendly language to gain fully informed consent and to increase stakeholder (youth) involvement and interest [39].

For the pilot study, all mentees (approximately 40) participating in four of the mentoring programs will be recruited to participate in the survey at the beginning and end of the program. The majority of these mentees have backgrounds from Syria and Eritrea, and almost all will be attending school. At the end of the six-month program, mentors (approximately 40) from these programs will also be invited to respond to a survey. All mentee respondents will receive small denomination gift cards (approximately $28) on completion of the surveys as a gesture of appreciation for their assistance with the project. We will also discuss how the youth perceive receiving gift cards, with a specific focus on any feelings of coerciveness, to make any adjustments before the RCT. Qualitative respondents will be selected from the individuals providing quantitative information to investigate specific aspects of program fidelity and implementation in more detail.

The full-scale RCT will recruit participants from Norwegian schools and include both a control and an intervention group. The study will try to select similar schools for both groups regarding school size, socioeconomic characteristics, and school type (age range of the student body). Within the intervention group of schools, intervention classes will be drawn randomly, whereas control classes will be drawn randomly from the control schools. Participants and nonparticipants will not attend the same schools to avoid contagion effects. The exact number of individuals will be estimated based on a power analysis of data from the pilot study and is anticipated to encompass several hundred youth. Half will be in the intervention group and half in the control group. Students who are not assigned to the control groups for the study will have the opportunity to receive the intervention after the study has concluded. Although all the youth will have a basic level of Norwegian proficiency, additional potential inclusion and exclusion criteria for the RCT will be developed based on findings from the pilot study. Similar to the pilot study, mentors will be surveyed at program conclusion, and respondents will be invited to qualitative interviews and focus groups, to supplement and nuance the quantitative data.

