### Data Collection Procedure

#### Pilot Study

After receiving information about the project in the form of a video and giving informed consent, the mentees will receive an individual link to participate in a Web survey. Questions on the mentee survey at program commencement will focus on social capital in the form of relationships with friends, native Norwegians, connectedness to the school environment, and to Norway more broadly. This will be used to test out and adjust measures for the full RCT study based on feedback from the groups. A Web survey will be administered at program completion, with the same survey questions as on the first survey, supplemented with questions about program fidelity (outputs) and a short battery to assess the relationship with the mentor and implementation. Mentors will receive surveys related to program fidelity and the relationship with mentees and staff. Additionally, both mentees and mentors will respond to survey questions on the usability of the digital platform. To supplement the quantitative survey data, qualitative data will be collected from mentors and mentees in interview form for both the pilot and RCT. Individuals will be selected for interviews based on characteristics such as age, sex, immigration background, and length of time in Norway, with a goal to get a very diverse group [38]. Interview questions will address barriers and facilitators to implementation, possible contextual factors relevant to the implementation and participants’ experiences of these factors, and the acceptability and meaningfulness of the measures used in the survey (see Outputs in the Measures section for details on the operationalization of these concepts). Questions to program staff will focus on resources such as program staffing, finances, and technical support for the digital platform.

The pilot study has been approved by the Data Protection Office at Oslo University Hospital. All pilot study data will be stored on a secure remote server as per Oslo University Hospital Personal Data Protection regulations. The pilot study is funded by a grant from the Norwegian Research Council and is a partnership between the Center for Shared Decision Making and Collaborative Care Research at Oslo University Hospital, NORCE-Norwegian Research Centre, Halmstad University, the Norwegian Labor and Welfare Administration (NAV), and Fretex.

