#### Full Study With Randomized Controlled Trial

The effects of the program as a social capital intervention will be studied using a two-level clustered randomized trial, with schools randomly assigned as intervention or control schools. The analyses will be at the individual level. In using a randomized comparison of mentees with non-mentees, the effects of mentoring on social capital can be assessed, also controlling for individual differences.

Youth in both the intervention and control groups will complete Web surveys. The youth surveys cover questions related to social capital and will be conducted at baseline (before program commencement), six months after the baseline measurement (at program completion for the intervention groups), and six months after program completion (12 months after the baseline measurement). Surveys to youth in the control group will be administered at the same time points as for the mentees. Mentors will respond to surveys at program conclusion. Because youth in the intervention group will receive mentoring outside of the school environment, we do not have a specific activity planned for the control group. However, control group youth will be put on a waiting list to participate in the mentoring program after study completion, if they desire. Approval from the institutional ethics board (Data Protection Officer) will be applied for and obtained before RCT study commencement.

The following table (Table 1) summarizes the instruments, respondents, and timeline for data collection.

**Table 1 table1:** Overview of the study procedure.

Study stage and data collection instrument		Respondents	Description	Time point

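### The only named source for the RCT's sample size and effectiveness cutoffs is an uncontrolled pilot of about 40 mentees, which cannot supply a between-arm effect or a usable school ICC

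*Protocol article*

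**What the plan says.** On sample size, Sample and Participant Recruitment states: "The exact number of individuals will be estimated based on a power analysis of data from the pilot study". The total "is anticipated to encompass several hundred youth", and "Half will be in the intervention group and half in the control group". The section gives the size as a number of youths and names no source other than the pilot.

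On cutoffs, Study Design says that the thresholds for fidelity "and effectiveness will be developed based on pilot study results".

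On the pilot, the survey covers "all mentees (approximately 40) participating in four of the mentoring programs", at the start and end of the program. Table 1 lists control youth in the RCT rows and none in the pilot rows. The Discussion says that pilot mentees self-select and that the findings may not generalise. The baseline survey is also a trial run of the instruments: "This will be used to test out and adjust measures for the full RCT study".

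On the RCT design, Full Study With Randomized Controlled Trial describes a "two-level clustered randomized trial, with schools randomly assigned as intervention or control schools", comparing mentees with non-mentees and analysed at the individual level.

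**The concern.** A power calculation for a school-randomised trial needs a between-arm difference worth detecting, an outcome SD, a school ICC, the number of schools and youths per school, and an attrition allowance. The protocol points to one source for the calculation, and that source cannot provide the first or the third of these.

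The pilot youths are in, or have completed, their first year of Norwegian schooling. The outcomes include comfort in speaking Norwegian, emotional connection to the country and the share of friends with a Norwegian background. These can plausibly move over six months without a mentor. With no control youth, that movement cannot be separated from the program's effect. If the change were read as the effect, the RCT could be too small. An effectiveness threshold derived from the same change would not be a criterion for a between-arm comparison.

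The four pilot clusters are mentoring programs, not schools. A trial sized in youths alone, without a defensible ICC, may have much less power than stated, and a null result would then be hard to interpret.

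**Working it through.** The protocol article gives no alpha, power, effect size, SD, ICC or number of schools, so there is no planned figure to reproduce. The check asks what a pilot of this size could supply.

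**Inputs from the document:** about 40 mentees, four programs, no pilot controls, 1:1 allocation, schools randomised.

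**Assumptions (not in the document):** two-sided alpha 5%, 80% power where N is computed, pre-post correlation 0.5, balanced pilot programs of 10, no attrition. For the power illustration: 300 youths, 20 schools (15 per school) and d = 0.35, without baseline adjustment.

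**1. Precision of the pilot change.**
- SE in SD units = sqrt(2 × (1 − 0.5)) / sqrt(40) = 0.158.
- An observed change of 0.30 SD has 95% CI 0.30 ± 1.96 × 0.158 = -0.01 to 0.61.
- Individually randomised total N = 4 × (1.96 + 0.8416)² / d², which is about 87 at d = 0.6, 349 at d = 0.3 and 3,140 at d = 0.1. All three values of d lie inside that interval.
- This is sampling error only. The bias from having no controls comes on top and cannot be measured from the pilot.

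**2. ICC, treating the four programs as if they were schools.**
- For an estimate of 0.05 with m = 10: F = 1 + 10 × 0.05 / 0.95 = 1.526, on 3 and 36 df.
- Dividing by the 97.5% and 2.5% F quantiles (3.505 and 0.0712) gives 0.4355 and 21.45.
- With ICC = (F − 1) / (F + m − 1), the limits are -0.06 and 0.67.
- If the true ICC were 0.05, about 41% of such pilots would give an estimate of zero or below.

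**3. What hangs on the ICC.** Design effect DE = 1 + (15 − 1) × ICC; SE = sqrt(4 × DE / 300); power from the non-central t with 18 df (critical value 2.101).

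| ICC | DE | SE | 0.35 / SE | Power |
|---|---|---|---|---|
| 0 | 1.00 | 0.1155 | 3.03 | 81.8% |
| 0.05 | 1.70 | 0.1506 | 2.32 | 59.5% |
| 0.10 | 2.40 | 0.1789 | 1.96 | 45.7% |

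**4. What the pilot can supply.** With n = 40, the 95% CI for an SD runs from about 0.82 to 1.28 times the estimate. Squared, that is a factor of 0.67 to 1.65 on N. This is usable as a rough guide with a margin, provided the measure does not change.

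**The case against.** The strongest reply is that the protocol does not say how the pilot data will enter the power analysis. It does not state that the pre-post change will be the assumed effect, or that clustering will be ignored, and it calls the trial a two-level clustered one. SD, correlation and retention are pilot data too, and a condensed article may leave the remaining inputs to a fuller document. This stands: a reader might infer that the trial will be undersized, and the text does not support that as a certainty. The harm is conditional on the effect or the ICC being taken from the pilot. What remains is that the pilot is the only source named for the trial's size, and that the effectiveness cutoffs are tied to pilot results in so many words.

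A reader might also infer that the fidelity cutoffs are circular, since the pilot is described as "allowing adjustments before the RCT if certain outputs are not achieved" while the cutoffs come from the same pilot. The documents do not support this. Background and Context and the Outputs section already state delivery requirements against which the pilot can be judged: six dyad meetings with one each month, training before the start, and the core components. Nothing says that the pilot-derived cutoffs will be applied back to the pilot. Assessing fidelity is the pilot's stated purpose, so using it to calibrate RCT cutoffs is legitimate.

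Finally, the power figures rest on assumed schools, N and d. The fall in power comes from clustering, not from the pilot as such. It shows how much depends on a quantity that the pilot cannot estimate. The protocol's acknowledgement of self-selection is fair, but it is not carried into the sample-size sentence.

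**Conclusion.** The point holds in conditional form and should be settled before RCT recruitment, which begins only after the pilot. The objection is to the suitability of the named source, not to the absence of a calculation. About 40 self-selected mentees in four programs without controls give no between-arm effect and no usable school ICC, and uncontrolled change is not a basis for an effectiveness cutoff. That conclusion follows from the design and needs no assumed values.

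The size of the consequence does depend on assumptions. In the illustration, power falls from about 82% to about 46% as the ICC goes from 0 to 0.10. Other values of N, d or number of schools, or adjustment for baseline, would change these figures. Whether the anticipated total is enough cannot be determined from this document, and the planned pilot cannot settle it.

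**What to change.** Replace the sample-size sentence in Sample and Participant Recruitment with text such as: *The RCT is sized by number of schools and youths per school, to detect a minimum important between-arm difference, set in advance on substantive grounds, on one designated primary social capital outcome. The school ICC is taken over a stated range (for example 0.02 to 0.10), power is quoted at the upper end, and an allowance is made for attrition. The pilot informs only the outcome SD, pre-post correlation and retention, with a margin for imprecision and for any measure changed after the pilot.*

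Do not take the consent rate from the pilot: its mentees volunteered for the program, and their uptake does not carry over to randomly drawn classes.

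In Study Design, remove effectiveness from the pilot-derived cutoffs. State that effectiveness will be judged by the between-arm difference and its confidence interval against the pre-set minimum difference. The fidelity cutoffs can stay as planned.

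The cost is planning text and a recalculation. The anticipated total may look less favourable once clustering and attrition are counted.
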